**Methods/Design:**

In a naturalistic study, 300 consecutive inpatient and 300 day hospital treatment episodes in seven psychosomatic hospitals in Germany will be included. Patients are assessed at four time points of measurement (admission, discharge, 3-months follow-up, 12-months follow-up) including a broad range of variables (self-report and expert ratings). First, the whole sample will be analysed to identify prognostic and prescriptive predictors of outcome (primary outcome criterion: Quick Inventory of Depressive Symptoms QIDS-total score, expert rating). Secondly, for a comparison of inpatient and day hospital treatment, samples will be matched according to known predictors of outcome.

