### Measurement time points

Time points of measurement will be the time point at admission (T0), at discharge (T1), a three months follow-up (T2) and a 12 months follow-up (T3). Data will include a detailed assessment on different levels: symptomatology (characteristics of depression and co-morbid conditions), general disturbance and quality of life, aspects of personality, interpersonal problems and a further aspects that has been identified to influence the course of depression: traumatic childhood experiences. Variables will be grouped into classes of possible predictors. A combination of self-report and assessments by independent, trained research assistants will be used (see Table 2).

**Table 2 T2:** Instruments used the INDDEP study

**Time point of measurement**	**Outcome/Variables**	**Patient**	**Research assistant**
		**(self-report)**	**(expert rating)**
**T0 **(admission)	Depressive symptomatology:	QIDS-SR	QIDS-C, SKID-I
	Co-morbidity		SCID I + II
	Personality, interpersonal problems, mode of coping:	IIP-32, DEQ, DAS	
	Overall disturbance and functioning:	SCL-90-R	SOFAS
	Social support:	F-SozU K-14	
	Quality of Life:	SF-12	
	Traumatisation:	CTQ	
**T1 **(discharge)		QIDS-SR	QIDS-C
		SCL-90-R	SOFAS
		IIP-32	
**T2 **(3-months Follow-up) and **T3 **(12-months Follow-up)		QIDS-SR	QIDS-C, LIFE-Interview
		SCL-90-R	SOFAS
		SF-12	
		IIP-32	

QIDS-SR = Quick Inventory of Depressive Symptoms, self-report form [23], QIDS-C = expert rating; SCID-I and SCID-II=Structured Clinical Interview for DSM IV axis I and II [24,25]; SCL-90-R = Symptom-Check-List 90-R [26]; DAS = Dysfunctional Attitudes Scale [27,28]; DEQ = Depressive Experiences Questionnaire [29,30]; SOFAS = Social and Occupational Functioning Assessment Scale [31]; IIP-32 = Inventory of Interpersonal Problems, 32-item version [32,33]; F-SozU K-14 = Fragebogen zur sozialen Unterstützung, 14-item version [34]; SF-12 = Fragebogen zum Gesundheitszustand (quality of life) [35]; CTQ = Childhood Trauma Questionnaire [36,37]; LIFE-Interview = Longitudinal Interval Follow-up Evaluation [38].

Note: Additionally assessed at all time points of measurement: pharmacological treatment, somatic diagnoses; at T0: previous treatment for depression; at T1: documentation of treatment received (dose, components); T2 and T3: further outpatient treatment, days of sick leave, number of contacts to health care system.

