### Statistical analysis

The statistical analysis will follow the example of Fournier et al. [22]. The continuous outcome (QIDS-C) will be analyzed with hierarchical linear models (HLM; nested random effects). The difference (T0-T2) will be controlled for baseline (T0) severity. Moderator and mediator analyses will be conducted according to Kraemer et al. [41]. The analysis of categorical outcome (remission classes) will be conducted with categorical regression with methods of optimal scaling (SPSS-CatReg) [42]. The identification of predictors with SPSS-CatReg is based on boot-strapping procedures or on the “Least Absolute Shrinkage and Selection Operators” [42]. For the HLM we will adapt the example of Fournier et al. [22] restricting the degrees of freedom of the selection of predictors in a hierarchical process.

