To study inpatient and day hospital treatments can be seen as a problematic task, as treatments consist of multiple therapeutic elements, are provided by different treatment teams and hospitals are embedded in different environments. We can only try to reduce bias as good as possible. To control for centre effects, each hospital has to recruit a minimum of 35 patients in each setting. Treatment components will be documented in detail (sort, duration, frequency), although in a pilot study we found treatment programs to be quite comparable in dose and composition of elements, due to German standards for psychosomatic clinic programs. We will take the nesting of data (settings, clinics) into consideration by using complex statistic methodology. But we cannot rule out that the fact of taking part in a study influences treatment course and has some sort of impact.

In terms of dropping out of the study, we expect rates to be low, as there are much more advantages for agreement to participate compared to a refusal: Patients will get in-depth diagnostic assessments and allowances for filling in the questionnaires or taking part in follow-up assessments (20€ for each time point of measurement). Furthermore, depressed patients usually are a group of patients with a comparably high compliance rate.

The principal investigators and participating centers are experienced in the conduction of studies and all hospitals provide the usual standard care of psychosomatic centres. Most of the hospitals have been involved in the preceding pilot study [5,21].

Overall, we think this study will provide important data on the treatment of depression in the German health care system and help to tailor treatment programs to the needs of different subgroups of patients.

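### Predictor selection in the QIDS-C hierarchical model names no internal validation, so weak moderators picked from the data are likely to be overstated

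*Protocol article*

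**What the plan says.** The Abstract (Methods/Design) puts predictor identification first and assigns it to all patients: "First, the whole sample will be analysed to identify prognostic and prescriptive predictors of outcome". The planned size is stated there too: "300 consecutive inpatient and 300 day hospital treatment episodes in seven psychosomatic hospitals in Germany will be included". No part of the sample is set aside for checking.

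The Statistical analysis section then names one selection route per form of the outcome.

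- **Continuous outcome:** "The continuous outcome (QIDS-C) will be analyzed with hierarchical linear models (HLM; nested random effects"). Predictors are chosen after the example of a cited study, by "restricting the degrees of freedom of the selection of predictors in a hierarchical process".
- **Categorical outcome (remission classes):** "The identification of predictors with SPSS-CatReg is based on boot-strapping procedures or on the" lasso.

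The number of candidates is not given. Measurement time points says "Variables will be grouped into classes of possible predictors", and Table 2 lists a dozen instruments at admission (counting the two QIDS forms and the two SCID parts separately), plus medication, somatic diagnoses and previous treatment. Predictors are sought both for general outcome and for differential outcome by setting. One moderator is stated in advance, under Objectives and hypotheses: introjective versus anaclitic type of depression.

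**The concern.** A restriction on degrees of freedom controls how many candidates are tried and in what order. It leaves untouched the coefficients and p-values of those that pass. When the same patients are used to choose an interaction and to estimate it, chance has helped the winners, and the reported sizes carry that help with them. The effect is worst for weak interactions, which pass only when the estimate happens to be large.

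This bears on a main aim of the study. The Discussion hopes that the results will "help to tailor treatment programs to the needs of different subgroups of patients". A moderator that is false, or twice its true size, would misinform that use. The plan already names a resampling tool, but only for the categorical form of the outcome.

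**Working it through.** The plan states no figure on this point, so there is none to reproduce. The check asks how much a staged selection on one data set distorts what it keeps.

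**Inputs from the article.** 300 + 300 = 600 patients. With 10% attrition, 600 × 0.9 = 540; with a further 20% mismatch loss, 540 × 0.8 = 432. The whole-sample analysis corresponds to 540, and 432 serves as a lower bound.

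**Assumptions, because the article gives no values.** 10, 20 or 30 independent candidates in blocks of five; equal groups; residual SD 1; within each block, backward selection at p < 0.20, 0.10, then 0.05; survivors refitted together at 0.05; estimates taken from the same patients. Ordinary regression was used, without centre clustering. There were 600 runs per setting, so a proportion near 60% has a simulation error of about √(0.6 × 0.4/600) = 2 percentage points.

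**No true moderator: runs that keep at least one false one**

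| Candidates | N = 432 | N = 540 | Independent tests, 1 − 0.95^k |
|---|---|---|---|
| 10 | 45% | 41% | 40% |
| 20 | 60% | 65% | 64% |
| 30 | 81% | 76% | 79% |

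Staging in blocks did no better than testing each candidate once at 0.05. The false moderators kept had a mean absolute interaction of 0.20 to 0.23 SD per SD of predictor. That is about the size of the standardised setting difference, 0.2, used in the sample size calculation.

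**20 candidates, 2 of them true: mean selected estimate divided by the truth (share selected in brackets)**

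| True interaction | N = 432 | N = 540 |
|---|---|---|
| 0.1 SD | 2.37 (17%) | 2.16 (20%) |
| 0.2 SD | 1.38 (53%) | 1.29 (61%) |
| 0.3 SD | 1.09 (87%) | 1.03 (93%) |
| 0.4 SD | 1.01 (98%) | 0.99 (99%) |

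**Cross-check by formula for one test, N = 540.** SE = 1/√(540 × 0.25) = 0.086. With δ = truth/SE, and neglecting the opposite tail, the mean of a selected estimate is SE × [δ + φ(1.96 − δ)/Φ(δ − 1.96)].

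- 0.10: δ = 1.16, selected 21% of the time, mean 0.086 × (1.16 + 0.290/0.212) ≈ 0.22, or 2.2 times.
- 0.20: δ = 2.32, mean 0.086 × (2.32 + 0.373/0.642) ≈ 0.25, or 1.25 times.
- 0.30: δ = 3.49, mean 0.086 × (3.49 + 0.125/0.937) ≈ 0.31, or 1.04 times.

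The formula and the simulation agree. For a prognostic main effect the SE is half as large (1/√540 = 0.043), so inflation is smaller at the same effect size. The concern is chiefly about moderators.

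**The case against.** The strongest reply is that the point rests on what a condensed article leaves out. It names no resampling for the hierarchical model, but rules none out. It says that it adapts a cited example and refers to a separate study protocol, neither of which is shown. A reader might infer that no validation will be done; the article does not support that. What remains is that the section does describe how predictors are selected for each form of the outcome, and what it describes for the continuous form does not address the estimates.

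Four further replies have force.

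- The restricted degrees of freedom are themselves a safeguard. They are, on the number of candidates tried. How strict they are depends on limits that the article does not give, and a tighter budget than the one simulated would let through fewer false moderators.
- A reader might infer that every reported moderator will be overstated. That is not so: inflation is 3% to 9% at 0.3 SD and about nil at 0.4 SD, and the introjective/anaclitic hypothesis carries no selection bias if it is tested whatever the selection finds.
- A reader might infer that the categorical analysis is fully protected. Bootstrap or lasso is stated there for identifying predictors, with no promise of corrected effects. The remission classes also derive from the same QIDS-C score, so one form of the main outcome already has a resampling or shrinkage step.
- The sentence on tailoring treatment is a closing hope. No decision rule is tied to any predictor, and the subgroup aim is described as observational.

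**Conclusion.** The point holds as a cheap improvement, and no error or contradiction in the plan is claimed. As the article describes it, selection and estimation for the continuous QIDS-C outcome take place on the same patients, and no internal validation is named. Data-selected weak moderators are then likely to be overstated, and some will be false.

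The false-moderator range of 41% to 81% depends on assuming 10 to 30 independent candidates, a final threshold of 0.05 and 432 to 540 patients. The inflation figures assume 20 candidates, the same threshold and the same patient range. A smaller candidate list or a stricter threshold would lower the chance of a false moderator. Weak interactions are a realistic case, since the sample size was set for differences between settings and not for interactions.

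**What to change.** In the Statistical analysis section, or in the analysis plan if it is still open:

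- Repeat the entire selection for the hierarchical model, every stage of it, in each bootstrap resample. Report each predictor's inclusion frequency and its optimism-corrected effect.
- Label predictors chosen from the data as exploratory.
- Test the introjective/anaclitic by setting interaction in a model fixed in advance, outside the selection.
- State the candidate list by class and the thresholds used at each stage.

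If the full protocol already provides for this, one sentence saying so is enough. Refitting with one of the seven centres left out at a time is a reasonable optional sensitivity analysis; it should not decide whether a predictor counts as identified.

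No further data are needed. The cost is analysis time, and probably fewer or smaller predictor effects to report.

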### Safety aspects and medical complications

There is a pseudonymisation of the data. At the end of the study, the data per centre will be made available to the participating centres who will remain owners of their own data sets. The coordinating centre (Freiburg) is responsible for data integrity and monitoring. Selected adverse events (like suicide attempts, transfer to other departments because of somatic problems or suicidal ideation) are defined in the study protocol, monitored and followed up constantly throughout the study and documented accordingly by the investigator including evaluation. Serious adverse events and other safety issues that might materially alter the current risk-benefit assessment should be reported by the coordinating investigator ([name], Freiburg) and to the responsible ethics committee according to the study protocol. As all patients get the usual standard treatment of routine care (observational study), criteria for ending the study because of adverse events are not applicable.

### Ethical issues

The final study protocol and the final version of the written informed consent form were approved by the ethics committee of the University of Freiburg as well as the local ethics committees. The trial will be carried out according to legal and regulatory requirements, the principles of good clinical practice and according to the Declaration of Helsinki.

## Discussion

The INDDEP study is a naturalistic study, which aims at the description of symptom courses in patients with depression receiving inpatient or day hospital treatment in psychosomatic clinics in Germany and the identification of subgroups by analyzing prognostic and prescriptive variables. Secondly, it aims at comparing effects of inpatient and day clinic treatment using a quasi-experimental design (matched samples).

A naturalistic design and broad inclusion criteria were chosen to achieve high external validity of data and to describe treatment and symptom courses in routine care. A randomized trial comparing inpatient treatment with outpatient or day clinic treatment would have led to a highly selective sample of patients having no treatment preference. It would have resulted in data on efficacy of treatments, but only in a small subsample. For a comparison of settings we choose to use the next best design: Inpatient and day hospital samples will be parallelized according to known predictors of outcome [14]. In the power calculation we took into consideration that sample size will be reduced by this procedure.

The INDDEP study is the largest study on inpatient and day clinic treatment in depression in the German health care system. In comparison to previous studies, it has the advantage that patients are diagnosed by structured interviews and followed up 3 and twelve months after discharge by self and expert assessments. Measurement is not limited to symptom change only, but comprises the evaluation on different levels relevant for overall functioning and quality of life: socio-demographic data, co-morbidity (mental, somatic), personality, coping strategies, interpersonal problems, traumatization and social support. Additionally, there will be a comprehensive documentation of the utilization of health care services after discharge, as well as a documentation of days of work absenteeism allowing an economic analysis.

To study inpatient and day hospital treatments can be seen as a problematic task, as treatments consist of multiple therapeutic elements, are provided by different treatment teams and hospitals are embedded in different environments. We can only try to reduce bias as good as possible. To control for centre effects, each hospital has to recruit a minimum of 35 patients in each setting. Treatment components will be documented in detail (sort, duration, frequency), although in a pilot study we found treatment programs to be quite comparable in dose and composition of elements, due to German standards for psychosomatic clinic programs. We will take the nesting of data (settings, clinics) into consideration by using complex statistic methodology. But we cannot rule out that the fact of taking part in a study influences treatment course and has some sort of impact.

In terms of dropping out of the study, we expect rates to be low, as there are much more advantages for agreement to participate compared to a refusal: Patients will get in-depth diagnostic assessments and allowances for filling in the questionnaires or taking part in follow-up assessments (20€ for each time point of measurement). Furthermore, depressed patients usually are a group of patients with a comparably high compliance rate.

The principal investigators and participating centers are experienced in the conduction of studies and all hospitals provide the usual standard care of psychosomatic centres. Most of the hospitals have been involved in the preceding pilot study [5,21].

Overall, we think this study will provide important data on the treatment of depression in the German health care system and help to tailor treatment programs to the needs of different subgroups of patients.

## Endnotes

^a^See for example: Psychotherapy Research, volume 20, number 1^st^ of January 2010.

## Abbreviations

HLM: Hierarchical linear models; MDE: Major depressive episode; QIDS: Quick Inventory of Depressive Symptoms.
